### Recruitment {15}

Recruitment will be carried out within the Department of Orthopedic Spine Surgery of Hôpital Privé Saint Martin in Bordeaux/Pessac. Patients with indications for arthrodesis of the thoracic and/or lumbar spine will be offered participation in the study during the V0 consultation where the information note will be delivered by the investigating surgeon.

About 500 patients per year are seen for this surgery within the establishment, and we estimate that at least 150 of them are likely to meet the inclusion criteria. The recruitment is estimated at 24 months.

### Assignment of interventions: allocation

#### Sequence generation {16a}

Before randomization, patients will be stratified according to the planned number of screws needed for surgery, with short-segment fusion comprising four to six screws (two to three vertebrae) and long-segment fusion comprising at least eight screws (more than three vertebrae). The randomization sequence will be generated before the commencement of the study separately for each stratum with the R software and will be integrated into the data management software (REDCap).

#### Concealment mechanism {16b}

The randomization sequences for each stratum will be concealed from the staff as well as from the patients.

#### Implementation {16c}

The patient will be randomized to a treatment arm only after inclusion, and the allocation will be based on a random number attributed to the patient’s electronic case report form (e-CRF), which is only accessible by the study staff.

### Assignment of interventions: blinding

#### Who will be blinded {17a}

This is an evaluator-blinded study, in which both the investigating surgeon and participant know which treatment is being administered. The only people blinded to the treatment arm are the two radiologists evaluating pedicle screw placement on postoperative CT images.

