### Trial design {8}

This is a single-centre evaluator-blinded RCT in a superiority framework with a 1:1 allocation ratio. There will be eight investigating surgeons, each of them capable of performing either intervention (robot-assisted and conventional). All the surgeons have equal experience performing robot-assisted arthrodesis and at least 5 years of experience performing conventional spine arthrodesis.

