### Outcomes {12}

The primary outcome of this study will be the rate of pedicle screws placed with grade A accuracy according to Gertzbein-Robbins classification (Table 1) in the robot-assisted versus conventional groups. The evaluation of the placement of the screws will be based on CT images from postoperative day 1 and will be carried out by two radiologists independent to the surgical team, blinded to the technique used for screw placement. In case of disagreement between the two evaluators, a 3rd evaluator will be requested.

**Table 1 Tab1:** Gertzbein-Robbins classification of pedicle screw placement

Grade A	fully intrapedicular position without breach of the pedicle cortex
Grade B	<2 mm cortical breach
Grade C	2-4 mm cortical breach
Grade D	4-6 mm cortical breach
Grade E	exceeding the pedicle cortex <6 mm or is outside of the pedicle

The secondary outcomes of the study will be as follows:Intervention time (min)OR occupancy time (min)LOS (days)EBL (volume of the suction jar at the end of the intervention in ml)Surgeon’s intraoperative radiation exposure (a dosimeter placed in contact with the surgeon’s clothing, in cGy/cm^2^)Signs of screw fracture/loosening (CT at 12 and 24 months postoperatively)Superior-level facet joint violation according to Babu-Mehta classification (Table 2; CT on postoperative day 1)Types of complications (neurologic, infectious, vascular, general, late and early mechanical complications) and complication rate at 24 months postoperativelyReoperation rate on the same instrumented level or one level above at 24 months postoperativelyFunctional and clinical outcomes at 3, 12 and 24 months postoperatively (pain on visual analogue scale [VAS; 0, best; 10, worst], ODI [0, best; 100, worst], HAD scale [0, best; 21, worst], sensory status with 3-point scale [0, absent sensation; 2, normal sensation], motor status with Medical Research Council’s [MRC] scale for muscle strength [0, no contraction; 5 full muscle strength])Cost-utility analysis based on medical costs and quality of life (QoL) evaluation (quality-adjusted life years [QALYs] derived from EuroQol [EQ-5D-5L questionnaire) at 12 months postoperatively

**Table 2 Tab2:** Babu-Mehta classification of facet joint violation

Grade 0	Screw not in facet
Grade 1	Screw in lateral facet but not in facet articulation
Grade 2	Penetration of facet articulation
Grade 3	Screw travels within facet articulation

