#### Procedure for unblinding if needed {17b}

The design is open-label with only outcome evaluators being blinded, so unblinding will not occur in any circumstances.

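### The blinding statement covers two radiologists only, so blinding of the third evaluator called in on disputed screws is not secured for the primary outcome

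*Protocol article*

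**What the plan says.** All references are to the protocol article.

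- **Design label.** Trial design {8}: "This is a single-centre evaluator-blinded RCT in a superiority framework with a 1:1 allocation ratio".
- **First two readers.** Outcomes {12} says that the grading of screws on the day 1 CT "will be carried out by two radiologists independent to the surgical team, blinded to the technique used for screw placement".
- **Third reader.** The next sentence of {12} reads: "In case of disagreement between the two evaluators, a 3rd evaluator will be requested". It does not mention this person's blinding or relation to the surgical team, or how the third read settles the grade.
- **Who is blinded.** Section {17a}: "The only people blinded to the treatment arm are the two radiologists evaluating pedicle screw placement on postoperative CT images".
- **Unblinding.** Section {17b}: "The design is open-label with only outcome evaluators being blinded, so unblinding will not occur in any circumstances".
- **Secondary CT outcomes.** {12} lists superior-level facet joint violation on the day 1 CT and "Signs of screw fracture/loosening (CT at 12 and 24 months postoperatively"). No reader is named for either.
- **Table 1.** Grades B, C and D are breaches below 2 mm, 2–4 mm and 4–6 mm. Grade E is given as "exceeding the pedicle cortex <6 mm or is outside of the pedicle".

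**The concern.** Surgeon and patient both know the allocation, so blinded reading of the day 1 CT is the main protection that the primary outcome has. That outcome needs one judgement per screw: breach of the cortex or none. Most screws are expected to be clear grade A. The screws on which two radiologists split between A and not A are the ones that call for a third opinion, and a reader who knows the arm has most room to lean on those.

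The blinding section is worded exclusively: it names two people and says that they are the only ones. This goes beyond a detail left to a reading charter. A centre could call in an arm-aware third reader and still comply with {17a} as written, while acting against {17b} and the evaluator-blinded label.

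Two smaller matters can be settled in the same edit. The blinding statement is tied to the grading of screw placement, so it does not clearly cover facet violation or the 12- and 24-month reads. Grade E as printed overlaps the grades below it.

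**Working it through.** **1. The sections side by side**

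| Reader | Outcomes {12} | Blinding {17a} | Unblinding {17b} |
|---|---|---|---|
| Two radiologists grading screws | Independent and blinded | Blinded | Blinded |
| Third evaluator | Called in on disagreement; nothing further stated | Outside the blinded group on the literal wording | Inside it, if an evaluator counts as an outcome evaluator |
| Readers of facet violation and fracture/loosening | Not named | Covered only if they are the same two radiologists, and then only by implication | Inside it, if they count as outcome evaluators |

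The second row is the conflict: one section excludes the third evaluator and another includes that person. Independence from the surgical team is stated for the first row only.

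**2. The plan's own figure**

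Inputs from Sample size {14}: 88% grade A in the conventional group and 7 points more with the robot (95%), ICC 0.3, an average of 5 screws per patient, 90% power, two-sided α 5%.

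- Unclustered n per group = (1.960 + 1.282)² × (0.88×0.12 + 0.95×0.05) / 0.07² = 328.3 screws.
- Design effect = 1 + (5 − 1) × 0.3 = 2.2.
- 328.3 × 2.2 = 722.3 screws, or 144.5 patients. Rounded up, 145 × 5 = 725 screws per group, as stated.

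The sample size reproduces, and the point does not depend on it. It supplies the planned effect and the standard error used below.

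**3. Possible size of the bias (assumed inputs)**

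The document gives no disagreement rate. Let q be the share of screws disputed across the A/not-A line, equal in both arms, and s the between-arm difference in the third reader's probability of calling a disputed screw A because the arm is known. If the third read settles the grade, bias in the difference = q × s.

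| q | s = 10 points | s = 20 points | s = 30 points |
|---|---|---|---|
| 5% | 0.5 | 1.0 | 1.5 |
| 10% | 1.0 | 2.0 | 3.0 |

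(Percentage points, against a planned effect of 7.)

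**4. How far q can go**

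The planned not-A rates are 12% and 5%, mean 8.5%. If each reader calls about 8.5% of screws not-A, overall A/not-A discordance cannot exceed 8.5% + 8.5% = 17%, and reaches that only if the readers never agree on a single not-A screw. Chance agreement is 0.915² + 0.085² = 0.844. So q = 5% gives kappa = (0.95 − 0.844)/(1 − 0.844) ≈ 0.68, and q = 10% gives kappa = (0.90 − 0.844)/(1 − 0.844) ≈ 0.36. A range of 5–10% therefore runs from good to rather poor agreement.

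**5. Effect on type I error**

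Take no true difference, 88% grade A and 725 screws per group. The effective number is 725/2.2 = 329.5 per group, and SE = √(2 × 0.88 × 0.12 / 329.5) = 2.5 points. The two-sided rejection rate is 1 − Φ(1.96 − bias/SE) + Φ(−1.96 − bias/SE):

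- bias 0.5 points: 5.4%
- bias 1.0 point: 6.8%
- bias 2.0 points: 12%
- bias 3.0 points: 22%

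**6. Table 1 and the primary outcome**

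As printed, a 1 mm breach satisfies both grade B and grade E. Both are not-A, so the overlap can create a dispute over grade but cannot change the primary outcome.

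**The case against.** The strongest reply is that nothing in the article says that the third reader knows the arm. {12} calls this person an evaluator, {17b} says that outcome evaluators are blinded, and the trial is labelled evaluator-blinded throughout. A condensed article may leave the adjudicator's details to the full protocol. This stands against several stronger readings that a reader might infer:

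- **That the third evaluator is unblinded and not independent.** The document does not say so. {17a} concerns blinding only, and the silence of {12} on independence does not state the opposite.
- **That this person decides every disputed screw.** {12} says only that a third evaluator will be requested. Majority, consensus and casting vote are all compatible with it.
- **That the secondary CT reads threaten the primary outcome.** They cannot affect the day 1 grade A proportion. Their readers are unnamed and may be the same two radiologists, particularly for facet violation, which uses the same scan. The secondary outcomes are declared exploratory in {20a}.
- **That the bias could be nearly as large as the planned effect.** That would need disputed shares of about 20%, above the 17% ceiling shown in the working, or larger shifts that nothing in the document supports.

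The reply does not remove the conflict. An omission could be left to the full protocol, but {17a} goes further by making an exclusive statement about who is blinded, and {17b} does not agree with it.

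**Conclusion.** The concern holds as an internal inconsistency. One section restricts blinding to two named readers, another adds a third reader for disagreements, and a third section implies that all outcome evaluators are blinded. Blinding and independence are therefore not secured for the reader consulted on disputed A/not-A screws, which bear directly on the primary outcome.

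The size is illustrative only. With 5–10% of screws disputed, a 10–30 point shift, equal disputed shares in both arms and a third read that settles the grade, the bias is 0.5–3 points against a planned 7. At the low end the effect on type I error is negligible (5.4%); at the high end it is not (about 22%). If the third evaluator is in fact masked, the bias from this source is nil and only the wording is at fault.

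The unnamed secondary CT readers and the grade E wording are lesser points with no bearing on the primary outcome.

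**What to change.** 1. In {12} and {17a}, state that the third evaluator is also independent of the surgical team and blinded to arm, and reads de-identified images. Replace the restriction to two radiologists so that {17a} agrees with {17b}.
2. State that facet violation on the day 1 CT and fracture/loosening at 12 and 24 months are also read blinded to arm, and by whom. This protects those exploratory outcomes.
3. Correct grade E in Table 1 so that it does not overlap B to D. Since D ends at 6 mm, the inequality sign appears to be reversed.

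Cost: the third reader is already planned, so no one has to be added. What remains is wording, masking of images already acquired, and a little more reading time for the secondary CTs. Recruitment began on 26/12/2022, so third reads may already exist. Any made with knowledge of the arm would have to be repeated by a masked reader.

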#### Procedure for unblinding if needed {17b}

The design is open-label with only outcome evaluators being blinded, so unblinding will not occur in any circumstances.

### Data collection and management

#### Plans for assessment and collection of outcomes {18a}

The following datasets will be defined:Intention-to-treat (ITT; effect of assigning the treatment): This dataset will include all enrolled patients who undergo surgery, who will be analysed in their assigned groups, irrespectively of possible protocol deviations or crossovers between treatment arms.Per-protocol (PP; effect of receiving the treatment): This dataset will include enrolled patients who undergo their assigned treatment without major deviations from the protocol (deviations that could impact the assessment of the primary endpoint).

The following information will be included on the e-CRF after enrolment and allocation:Patients’ characteristics: age (years), sex, weight (kg), height (cm) and pregnancy testRadiological data: screw placement accuracy, screw fracture/loosening and superior-level facet joint violation on CT images on postoperative day 1 and at 12- and 24-months follow-upClinical data: intervention time, LOS, EBL, surgeon’s intraoperative radiation exposure, sensory and motor function at inclusion and all follow-up visitsFunctional outcomes: pain, ODI, HAD, EQ5D-5L at inclusion and all follow-up visitsMedical costs at 12 months follow-up

The primary outcome will be assessed for both datasets (ITT and PP). The secondary outcomes will be assessed on the ITT dataset.

#### Plans to promote participant retention and complete follow-up {18b}

The data for the primary outcome (pedicle screw placement accuracy) will be collected on postoperative day 1, so the risk of missing data is small. For the analysis on the ITT dataset, if the evaluation of the placement of a screw is missing, it will be considered that the screw is not correctly placed. If the evaluation of all screws is missing for one patient, the patient will not be analysed, although the patient will still be included in the initial cohort. All the other data are considered secondary outcomes; the missing data will be reported as such in the final analysis. Outcomes will be collected for all the patients regardless of possible protocol deviations or crossovers between treatment arms.

If a patient withdraws prematurely from the study, they will not be replaced, and reasons for patient withdrawal must be documented. For patients lost to follow-up, attempts to contact the patient must be made and documented. No further outcomes will be collected from the patients who discontinue participation in the study.

#### Data management {19}

The data collected will be taken from each patient file completed by the investigating surgeon during medical visits. They will be then transferred to a secure database (REDCap). Patient data will be anonymized before being entered into the database, assigning each patient a unique ID number, so that duplicates can be checked later. An input mask will be established to initially configure the type of variables to be entered and its modalities. Health data will be collected through a validated e-CRF of REDCap software, meeting Title 21 Code of Federal Regulation Part 11 and hosted on REDCap’s health data certified servers, meeting all the levels of security required by the Food and Drug Administration (FDA), European Medicines Agency (EMA) and in compliance with the General Data Protection and Regulation (GDPR).

#### Confidentiality {27}

In accordance with the legal provisions in force (articles L.1121-3 and R.5121-13 of the Public Health Code [PHC]), persons having direct access to the source data will take all the necessary precautions to ensure the confidentiality of the information relating to experimental drugs, to research, to the patients who take part in it and in particular with regard to their identity as well as to the results obtained. These persons, like the investigating surgeons themselves, are subject to professional secrecy.

During the biomedical research or at its end, the data collected (on the patients who agree to it) and transmitted to the sponsor by the investigating surgeons (or any other specialized stakeholders) will be made anonymous. Under no circumstances should they clearly show the names of the patients concerned or their addresses.

Each patient will be assigned a confidential identification code, made up of the investigating surgeon centre number (two digits), a two-letter code (first name initial + last name initial) and the patient’s inclusion order number in the centre (three digits).

The sponsor will ensure that each patient who agrees to the research has given their written consent for access to the individual data concerning them, which is strictly necessary for the quality control of the research.

#### Plans for collection, laboratory evaluation and storage of biological specimens for genetic or molecular analysis in this trial/future use {33}

Not applicable as no biological samples will be collected for future analysis.

## Statistical methods

### Statistical methods for primary and secondary outcomes {20a}

The quantitative variables will be described by the number of values entered, the number of missing data, the mean, the standard deviation, the median, the 1st and 3rd quartiles, the minimum and the maximum. The qualitative variables will be described by the number of values entered, the number of missing data, the frequency, the percentage of each modality and the 95% confidence interval (CI) of each modality, if relevant. The type I error (*α*) is set at 5% with a two-tailed analysis for the entire study. No management of multiplicity will be carried out. The secondary outcomes will be analysed on an exploratory basis. The primary outcome (proportion of grade A placed screws according to Gertzbein-Robbins classification on postoperative day 1) will be described by group (robot-assisted vs. conventional surgery) and compared using a marginal logistic model (taking into account screw clusters in the same patient) including the group and the randomization stratification factor (long-segment fusion vs. short-segment fusion). The results of the marginal logistic model will be interpreted in terms of adjusted odds ratio (aOR) accompanied by the 95% CI. Intervention time, OR occupancy time, LOS, EBL and surgeon’s intraoperative radiation exposure will be described by group (robot-assisted vs. conventional surgery) and compared using an analysis of variance (ANOVA) including the group and the randomization stratification factor (long-segment fusion vs. short-segment fusion). Radiological stability (signs of screw fracture/loosening), superior-level facet joint violation, complication and reoperation rates will be compared using logistic regression including the group and the stratification factor of the randomization (long-segment fusion vs. short-segment fusion). Functional outcomes (ODI, pain, HAD) will be compared using an analysis of covariance (ANCOVA) including the group, the score at inclusion and the randomization stratification factor (long-segment fusion vs. short-segment fusion); this analysis will be carried out at each evaluation time (3-, 12- and 24-month follow-up). The evaluation of sensory status and motor status will be compared using a Cochran-Mantel-Haenszel test including the group and the stratification factor of the randomization (long-segment fusion vs. short-segment fusion); this analysis will be carried out at each evaluation time (3-, 12- and 24-month follow-up). The cost-utility analysis will be carried out according to the recommendations of the French National Authority for Health (HAS) [11], based on QALYs (lifespan weighted by health-related quality of life), derived from the EQ5D-5L. All direct medical costs will be measured over 12 months following hospital discharge. The incremental cost-utility ratio (difference in costs divided by the difference in QALYs) between robot-assisted surgery and conventional surgery will be determined at 12 months along with their 95% CIs. All statistical analysis will be performed using the latest version of the SAS software.

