### Sample size {14}

Patients are considered as “clusters” of screws, due to the inter-dependence on the placement of screws in the context of complex cases (e.g. morbid obesity, bone fragility). The required sample size of screws is calculated to compare the proportions of grade A placed screws (Gertzbein-Robbins classification) by robot-assisted versus conventional surgery in thoracolumbar arthrodesis. According to the literature, the proportion of grade A placed screws of conventional surgery is approximately 88% [3, 8], and we hypothesize that robot-assisted surgery will improve this proportion by 7%. Therefore, 725 screws per group are needed to detect a statistically significant difference in the proportion of grade A placed screws, assuming an intracluster correlation coefficient (ICC) of 0.3, with a power of 90% and a bilateral *α* of 5%. Based on the assumption that each patient is implanted with an average of 5 screws [4, 9, 10] and that 5% of patients will be randomized but not operated, the total number of patients to be randomized is 300 (150 patients per group). The sample size was determined using the Power Analysis & Sample Size (PASS) software 2021 (NCSS).

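### Sensory and motor status are compared at each visit without the inclusion values that the trial collects, at some cost in precision

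*Protocol article*

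**What the plan says.** All references are to the protocol article.

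- **When measured.** Table 3 in Participant timeline {13} marks sensory status and motor status at the inclusion visit and at 3, 12 and 24 months. Section {18a} also lists both at inclusion and at every follow-up visit.
- **Where they belong.** Outcomes {12} places them in one family of functional and clinical outcomes with pain, ODI and HAD. Sensory status has three levels (0 to 2). Motor status uses the MRC scale (0 to 5).
- **How they are analysed.** Section {20a} states: "The evaluation of sensory status and motor status will be compared using a Cochran-Mantel-Haenszel test including the group and the stratification factor". The stratification factor is short- versus long-segment fusion, and the test is repeated at each visit.
- **How the rest of the family is analysed.** In the preceding sentence of {20a}, ODI, pain and HAD get an ANCOVA "including the group, the score at inclusion and the randomization stratification factor".
- **Status.** Section {20a} calls the secondary outcomes exploratory, with no multiplicity control. The type I error "is set at 5% with a two-tailed analysis for the entire study".

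**The concern.** Two adjacent sentences specify parallel analyses for one outcome family, and only one of them uses the inclusion value. The covariates are named in both, so this is a stated choice and not detail left to a later plan. No reason is given for the difference.

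The eligibility criteria {10} admit any indication for thoracic or lumbar arthrodesis and do not exclude patients with an existing neurological deficit. A follow-up score taken alone does not show whether a deficit is new, old or partly recovered. If one arm happens to start with more deficits, part of that difference reappears at 3, 12 and 24 months and sits in the group comparison. Even with balanced arms, variation between patients that the inclusion value could explain stays in the error term.

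**Working it through.** **The plan's own figure, and the number per arm.** Inputs from Sample size {14}: "the proportion of grade A placed screws of conventional surgery is approximately 88" per cent; "we hypothesize that robot-assisted surgery will improve this proportion by 7" per cent, read as 0.88 against 0.95; "assuming an intracluster correlation coefficient (ICC) of 0.3"; "with a power of 90% and a bilateral" α of 5%; on average 5 screws per patient; 5% randomised but not operated; 150 patients per group.

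- Independent screws per group: 328.3 (unpooled variance) or 332 (pooled).
- Design effect: 1 + (5 − 1) × 0.3 = 2.2.
- Screws per group: 328.3 × 2.2 = 722, or 332 × 2.2 = 730. The stated 725 reproduces.
- Patients per group: 725 / 5 = 145, and 145 / 0.95 = 153, close to the stated 150.
- Operated patients per arm: 150 × 0.95 = 142.5.

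This point does not change any of these figures. The plan gives no figure for sensory or motor status, so the rest relies on assumptions.

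**Chance imbalance at inclusion.** In SD units, the SE of the difference between arms is √(2 / 142.5) = 0.118, so the 95% limit is 1.96 × 0.118 = 0.23 SD. Loss to follow-up by later visits would widen this.

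**What carries through.** Let r be the correlation between inclusion and follow-up scores. The expected carry-over of an imbalance d is r × d. Linear adjustment multiplies the variance by 1 − r², which is equivalent to 1/(1 − r²) − 1 more patients. The documents do not give r; 0.3 to 0.7 is an assumption.

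| r | Carry-over of a 0.232 SD imbalance | Variance factor | Equivalent extra patients |
|---|---|---|---|
| 0.3 | 0.07 SD | 0.91 | 10% |
| 0.5 | 0.12 SD | 0.75 | 33% |
| 0.7 | 0.16 SD | 0.51 | 96% |

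**What this means for a CMH test on a short scale.** The linear factors do not transfer directly to three categories, so the test itself was simulated: 4,000 trials per setting and 285 operated patients in total. Assumptions: 30% long-segment fusion, a latent normal score cut at −1.8 and −0.5, r as the correlation of the latent scores, a latent effect of 0.4 SD, and the mean-score form of the CMH test. One analysis stratifies by fusion length only; the other also by inclusion category.

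| r | Type I error, fusion only | Type I error, plus inclusion | Power, fusion only | Power, plus inclusion |
|---|---|---|---|---|
| 0.3 | 5.5% | 5.5% | 70% | 71% |
| 0.5 | 4.6% | 4.9% | 70% | 75% |
| 0.7 | 5.0% | 4.7% | 71% | 82% |

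The simulation SE of one power figure is √(0.7 × 0.3 / 4,000) = 0.007, so the gain at r = 0.3 is hardly more than none. The gains at 0.5 and 0.7 are real. The simulated scale matches the sensory item; the six-level MRC scale was not simulated.

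**The case against.** The case for leaving the plan alone has four parts.

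- **The test is valid.** Randomisation balances earlier deficits in expectation, and the simulated type I error is 4.6% to 5.5% under either analysis. This stands. A reader might infer that ignoring the inclusion status biases the comparison or invalidates the test. It does neither; the loss is in precision and in how one unlucky allocation reads.
- **New deficits have their own route.** Outcomes {12} lists neurologic complications separately, {20a} compares complication rates by logistic regression, and section {22} names sensory and motor deficits among the expected surgical events. This stands too, so the trial would not lose sight of surgical nerve injury. It does not repair the three sensory and motor comparisons.
- **The size is easily overstated.** Suppose 20% of patients have a deficit at inclusion (an assumption). The SE of the chance difference is √(2 × 0.2 × 0.8 / 142) = 0.047, so the 95% limit is about 9 percentage points. A reader might take all 9 points to enter the follow-up comparison. That needs baseline status to persist completely; with r of 0.3 to 0.6 it is about 3 to 6 points (0.3 × 9.3 = 2.8; 0.6 × 9.3 = 5.6).
- **The remedy is not perfect.** Sparse levels may have to be merged, and an ordinal model estimates a conditional effect and needs its proportionality assumption checked. These are reasons to choose the form of adjustment with care, not to discard the inclusion value.

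The exploratory label lowers the stakes, but it does not explain why these two outcomes are treated differently from ODI, pain and HAD.

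**Conclusion.** The point holds for sensory and motor status, as a minor improvement. The analysis is valid but less precise than the collected data allow, and it is out of step with the protocol's own handling of ODI, pain and HAD. The size depends on an undocumented correlation: at 0.3 the loss is negligible, and at 0.7 it is about 11 power points under the assumed three-level scale. The primary outcome and the 300-patient sample size are not affected.

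Two extensions are tempting, and the documents do not support them as defects.

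- **Operative outcomes.** Intervention time, room occupancy, stay, blood loss and radiation exposure are "compared using an analysis of variance (ANOVA) including the group and the randomization stratification factor". They have no inclusion value to adjust for, and fusion length, a grouping of the planned screw number, is already in the model. The exact planned number of screws could reduce residual variance, but it does not appear in the e-CRF list in {18a}. It is at most an optional refinement, if the count is recorded.
- **QALYs.** EQ-5D-5L is collected at inclusion. Section {20a} refers the cost-utility analysis to the French health authority's recommendations and neither states nor excludes adjustment for baseline utility. Silence in a condensed article is not a decision against it.

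**What to change.** In {20a}, or in the SAP if it is still open, choose one of these for sensory and motor status at each visit:

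- Keep the CMH test and stratify it by inclusion category as well as fusion length, with a rule for merging sparse levels that is fixed before outcome data by arm are seen. This is the smaller change and keeps the planned framework.
- Use an ordinal regression with group, inclusion status and fusion stratum. This also gives an effect estimate, but proportionality must be checked.

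If the SAP already includes the inclusion category, the two descriptions only need to be aligned. The cost is wording and a few lines of code: no new data, visits or patients.
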